### Protocol adherence

Practitioner who deliver the intervention are trained using a standardized system of training and accreditation, designed to promote program use and fidelity. Sessions are delivered according to a standardized manual and practitioners received regular clinical supervision. Each practitioner will complete a protocol adherence checklist for each session conducted, which will be coded by a research assistant who is independent of the delivery of the sessions but familiar with the intervention and protocols for adherence. Using structured session checklists, videotapes of group sessions will be independently coded for protocol adherence. A second rater will code 25% of the sessions to establish inter-rater reliability (kappa).

### Assessment

Table 1 provides an overview of the assessment measures and the time points at which they are assessed. All parent-report measures will be provided in a written (online or printed) self-administered questionnaire format, and will take approximately 30 to 40 min to complete. Most of the measures used have been previously validated and are commonly used. Socioeconomic status (e.g., income, occupation status, parent education), age, history of mental illness and ethnic background will be assessed using the *Family Background Questionnaire* [61]*.* Only the mother will complete this measure, as well as the *Cambridge Worry Scale* [CWS; 68].

**Table 1 Tab1:** Summary of Assessment Measures

Construct	Assessment Measure	Time Point
Demographics	*Family Background Questionnaire*	T1
Primary Outcomes		
Parental Confidence	*Maternal Self-Report Inventory*	T1, T2, T3
Parental Self-Efficacy	*Maternal Efficacy Questionnaire*	T2, T3
Secondary Outcomes		
Parental Mental Health		
Depression	*Edinburgh Postnatal Depression Inventory*	T1, T2, T3
Anxiety	*Depression Anxiety Stress Scale 21*	T1, T2, T3
Pregnancy Worry (mothers only)	*Cambridge Worry Scale*	T1, T2, T3
Life Satisfaction	*Oxford Happiness Questionnaire*	T1, T2, T3
Expectations	*Prenatal Maternal Expectations Scale*	T1
Family and Social Support		
Couple Relationship	*3 items from PAFAS, 2 items from HCTC & 1 overall item*	T1, T2, T3
Social Support	*Social Support Scale*	T1
Mother-Child Relationship		
Maternal Responsiveness	*Maternal Infant Responsiveness Inventory*	T2, T3
Observed Mother-Infant Responsiveness	*The Care Index*	T2, T3
Mother-Child Bonding	*Postpartum Bonding Instrument*	T2, T3
Baby Outcomes		
Problematic Behaviors	*Baby Behaviour Inventory*	T2, T3
Baby Behaviors	*Baby Diary*	T2, T3
Other		
Parent Involvement	*Attendance at group sessions (intervention only)*	During group sessions
Conflicting Advice & Problem Solving	*6 items*	T1, T2, T3 (problem solving only T2 and T3)
Strategies used	*Strategies Checklist*	T2 (intervention only), T3
Services accessed		T2, T3
Client Satisfaction	*Client Satisfaction Scale*	T2

The CWS will only be completed by the mother because several items focus on the pregnancy and birth, thus this scale would not be appropriate for fathers. Both mother and father will complete all other self-report measures. Most of the validated scales were written for mothers to complete, thus wording will be slightly changed to suit the father’s perspective. Where available, internal consistencies from previous studies for mothers and fathers are reported below. Unless otherwise stated, if only one internal consistency is reported, it would refer to mothers’ data only. The home observation will only be conducted with the mother and the baby.

### Primary outcome measures

#### Parenting confidence and sense of competency

The *Maternal Self-Report Inventory* [62] is an overall measure of self-esteem related to the adaptation of motherhood, which has a total of 100 questions across seven subscales. This study will use only the 8-item *General Ability and Preparedness for Mothering Role* subscale of the 26-item short form of the questionnaire. The 5 point scale ranges from 1 = *completely false* to 5 = *completely true.* This subscale has good internal consistency (α = .88). The full scale has demonstrated acceptable external validity [62].

The *Maternal Self­Efficacy Scale* [MSES; 40] is a 10-item measure capturing parent’s self­efficacy and perceived behavioral competence among mothers of infants in the first year. It has previously been used with clinically depressed and non­depressed mothers of infants aged three to 13 months. Nine of the ten items address mother’s feelings of competence in relation to specific domains of infant care, for example soothing the baby, understanding what the baby wants, amusing the baby, disengaging from the baby, performing daily routine tasks, such as feeding, changing and bathing the baby. A final tenth item taps mother’s global feelings of efficacy in mothering. Responses are recorded on a 4-point scale from 1 = *not good at all* to 4 = *very good.* This subscale has good reliability [α = .86; 40, α = .75 and .84, respectively for fathers and mothers; 58] and demonstrated good concurrent validity to the Parenting Sense of Competence Scale [40].

### Secondary outcomes

#### Parental well-being

The *Edinburgh Postnatal Depression Scale* [EPDS; 63] is a 10-item scale and is widely used to screen for parental depression during pregnancy and post-birth. Expectant mothers and fathers are asked to indicate how often they have experienced symptoms relating to depression and/or anxiety over the previous seven days. The response scale is from 0 = *no, not at all* to 3 = *yes, all the time*. The EPDS has good internal consistency for mothers [α = .87; 63] and fathers [α = .81]; [63]. The scale’s sensitivity in detecting depression has been shown to be between 80 and 100% [64, 65].

The *Depression, Anxiety and Stress Scale 21* [66] is a 21-item measure assessing symptoms of depression, anxiety and stress in adults. This study will only use the anxiety and stress subscales. The 4 point response scale is from 0 = *did not apply to me at all, never*, to 3 = a*pplied to me very much, or most of the time, almost always*. The measure has good reliability for the anxiety (α = .81) and stress (α = .88) subscales for both men and women together. The scale demonstrated good convergent validity with the Mood and Anxiety Symptom Questionnaire 90, the Perceived Stress Scale and the Beck Anxiety Inventory [67].

The *Cambridge Worry Scale* [68] is a 17-item prenatal measure assessing worries and concerns in relation to pregnancy. Items assess concerns about health, worry about labor and birth, worry about the baby and concerns about relationships. The 6 point response scale is from 0 = *not a worry* to 5 = *major worry.* The scale has satisfactory internal consistency (α = .79), and good convergent validity with the trait form of the State-Trait Anxiety Inventory [68].

The *Oxford Happiness Questionnaire* (OHQ; Hills & Argyle, 2002) is an 8-item measure assessing personal happiness, based on the original Oxford Happiness Inventory [69]. The 6 point Likert Scale is from 1 = *strongly disagree* to 6 = *strongly agree*. The scale has shown high internal consistency (α = .91) for both men and women, and good convergent validity with variety of measures related to happiness and satisfaction with life [70].

The *Prenatal Maternal Expectations Scale* [71] has 46 items and assesses prenatal expectations pertaining to the following subdomains: characteristics of the baby and child care; degree of enjoyment anticipated in association with parenting, expected changes in the parent’s significant relationships resulting from becoming a parent, anticipated changes in lifestyle or quality of life associated with the parental role, and projected image of self as a parent. Responses are made on a 5 point scale from 1 = *strongly agree* to 5 = *strongly disagree.* The scale has good reliability (α = .83) and predictive validity [71].

#### Family and social support

The *Social Support Scale* [72] will be used to assess participants’ satisfaction with their social network. Two out of the four items will be used for this study. The first item asks participants how satisfied they are with the extent of formal support (i.e., health professionals) they currently receive. The second item referred asks participants how satisfied they are with the extent of informal support (i.e., provided by family, friends and neighbors) they currently receive (from 1 = *Not at all satisfied* to 5 = *Completely satisfied).*

The *Couple Relationship* will be assessed using three items from the Parenting and Family Adjustment Scale [PAFAS]; [73], two items from the Household and Childcare Task Checklist [74] measuring overall perceived fairness and satisfaction with the division of tasks, and one overall item on global relationship satisfaction from the *Relationship Quality Index* [75]. For the purpose of the current study, the PAFAS items assessing the couple relationship were slightly reworded to suit the context of expecting/ having a baby.

For both the social support and couple relationship measures, only a selected few items were chosen to be included in order to limit the total length of the questionnaires. The social support measure and one item from the couple relationship measure were intended as a risk factor indicator only to be used for edibility assessment, rather than an outcome measure.

#### Mother-child relationship

The *Maternal Infant Responsiveness Instrument* [76] is a 22­item scale designed to measure the parents’ feelings about the infant and an appraisal of the infant’s responses. Specifically, it measures the parent’s recognition of his/her own responses, the parent’s recognition of the infant’s responses to him/her, and any difficulties they notice in responsiveness. Response options are from 1 = *strongly agree* to 5 = *strongly disagree.* Internal consistency of the measure is good [α = .81 and .88 for mothers and fathers respectively; 58, α = .86 for mothers; 75].

The *Postpartum Bonding Instrument* [77] will assess parent­infant bonding difficulties. This 25–item scale asks parents to rate how often a list of positive and negative thoughts/ emotions are true for them, from 1 = *always* to 6 = *never*. The PBI has four subscales, which reflect impaired bonding, rejection and anger, anxiety about care and risk of abuse. Internal consistency is acceptable (α = .76) and the measure demonstrated good convergent and concurrent validity [78].

##### The *Care Index*

A home observation will be carried out with the mother and the baby at two stages; upon completion of the program and six months post birth. This will not be done with fathers, as scheduling these visits with fathers will not be practical given that most will be in full-time employment. It will be carried out within the context of semi­structured play and naturalistic interaction, lasting approximately 15 min. Mothers will be instructed to interact with their baby as they usually would. With the baby beside her, the mother will first be asked to read an information sheet and the Baby Triple P brochure for 2 min. This is followed by a nappy change lasting 3 min. The mother will then move on to free play with the baby, using age appropriate toys brought by the researcher. After 5 min, the researcher will prompt the mother to leave the room briefly for a maximum of 2 min. This can be reduced to 20–30 s if the baby is upset and is not able to settle on his or her own. Lastly, the reunion context will be recorded for 2 min. Observations will be videotaped. Video recording of the mother’s interaction with the baby (i.e., the 5 min component) will be coded using the *Care Index* [79]. The *Care Index* assesses mother-infant interaction from birth to about two years of age based on a short, videotaped play interaction of 3–5 min (from the five minute play time segment). Trained independent coders will conduct this assessment, who will be blind to the study aims. The CARE-Index is a dyadic procedure that assesses adult sensitivity in a dyadic context. The measure assesses mothers on three scales: sensitivity, control and unresponsiveness. There are also four scales for infants: cooperativeness, compulsivity, difficultness, and passivity. Validity has been demonstrated with the Parent-infant Interaction Observation Scale [80]. Reliabilities will be assessed by calculating the inter-rater reliabilities for a random 25% of the coding between the two coders.

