### Care as usual

Couples in CAU will complete assessments at baseline, ten weeks post birth, and at six months post birth. These are the same time points at which the intervention group complete their assessments. During this time, families will continue to receive regular primary care and other pre and post-natal services, as appropriate, including antenatal classes, which may be offered at the mother’s hospital, as well as other services provided by GPs or obstetricians. These services were also available to mothers in the Baby Triple P group. Other than regarding issues of assessment, these parents will have no contact with the research team, but are free to access support from other community services and will be given appropriate referral information should they ask for assistance. After the 6-month follow-up assessment, families will be offered the Baby Triple P workbook.

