A few limitations of this study should be kept in mind. First, the majority of the assessments are self-report questionnaires, which rely on participant’s honesty, accurate self-reflection and memory of events, as well as their understanding and interpretation of the questions. They also are affected by social biases. However, the inclusion of the observational assessment of responsiveness using the Care Index aims to combat some of the biases of the self-report measures. Another limitation could be the use of a care as usual control group in place of an attention-placebo comparison, as any possible changes after the intervention might be due to the additional support and attention received from the facilitator rather than the specific content of Baby Triple P. However, we have included a strategy checklist to identify if and which of the strategies parents are using, and we can therefore ascertain differences between the groups due to the extent the Baby Triple P strategies are utilized. This would be a good indicator that the intervention itself leads to changes in the outcomes. Furthermore, the use of an attention-placebo control group has it’s own limitations in preventative parenting intervention research, such as unequal drop outs in the control group arm and ethical dilemmas when unsafe parenting behaviors are discussed among parents [90].

Recruitment and enrolment to the study commenced in January 2014 and closed in March 2015. Follow-up data collection was completed in January 2016. During the design phase of this study, the other trials on Baby Triple P discussed earlier were ongoing and results have only become available during the course of this trial. Results will be published in a peer-reviewed journal when analyses are completed. It is expected that participating in a group-based preventative parenting intervention has the potential to help new parents adjust to the transition to parenthood more easily by improving parenting confidence, competence, the parent-infant relationship, parent wellbeing as well as reducing baby behavior problems.

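### The home-visit script has mothers, apparently in both arms, read the Baby Triple P brochure shortly before the interaction scored with the Care Index

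*Protocol article*

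**What the plan says.** The Care Index section of the protocol article sets out one visit script. At the start, "the mother will first be asked to read an information sheet and the Baby Triple P brochure for 2 min". Then "This is followed by a nappy change lasting 3 min". After that, "The mother will then move on to free play with the baby, using age appropriate toys brought by the researcher". The scored material is the play segment: "Video recording of the mother’s interaction with the baby (i.e., the 5 min component) will be coded using the" Care Index. The visit takes place "at two stages; upon completion of the program and six months post birth", that is, at T2 and T3 in Table 1. On coding: "Trained independent coders will conduct this assessment, who will be blind to the study aims".

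The Care as usual section puts control couples on the intervention group's assessment schedule and limits their contact with the research team to assessment matters. It adds: "After the 6-month follow-up assessment, families will be offered the Baby Triple P workbook".

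The Discussion relies on this measure. It says that including the Care Index "aims to combat some of the biases of the self-report measures".

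**The concern.** An observed outcome protects against self-report bias only if the observation itself does not disturb the comparison between arms. This script opens with a text that carries the name of the programme under test, in a visit otherwise meant to capture the mother's ordinary behaviour with her baby.

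Two effects are possible, and they pull in opposite directions. A control mother may pick up something from the brochure, which would shrink the difference between arms. An intervention mother may be reminded of what she was taught just before she is filmed, which would enlarge it.

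The T2 reading also precedes everything measured at T3. That includes both primary measures at six months and the strategies checklist, which controls complete only at T3. The Discussion uses that checklist to argue that differences between arms reflect the programme's content rather than attention. The only between-arm comparison of strategy use therefore comes after controls have been shown the brochure.

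**Working it through.** The plan gives no figure to reproduce on this point. The check sets the passages side by side and adds up the stated times.

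**Timeline of one visit (Care Index section).**
- Reading: minute 0 to 2.
- Nappy change, 3 min: minute 2 to 5.
- Free play, 5 min, the coded part: minute 5 to 10.
- Gap between the end of reading and the start of scoring: 5 − 2 = 3 min.

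**Amount of exposure.**
- Two visits × 2 min = 4 min in all, shared with the information sheet.
- Programme time (Intervention section): 4 × 120 min + 4 × 30 min = 600 min.
- Ratio: 4 / 600 = 0.67%.

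**Do controls follow this script?** No single sentence says so, but four places point that way.
1. The script speaks of the mother without naming an arm and describes no alternative reading.
2. The Care as usual section gives both arms the same assessment time points.
3. Table 1 lists the Care Index at T2 and T3 without the intervention-only mark that it gives to attendance and to the T2 strategies checklist.
4. The Primary analyses section includes the observational assessment among the data used to compare the arms, so controls must be observed.

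Two details weaken this slightly. The first visit is timed by completion of the programme, which has no literal meaning for controls. The marks in Table 1 are also not complete: the client satisfaction row has none, although the text gives that measure to the intervention group only. Neither detail suggests a separate script for controls.

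**Does this contradict the CAU description?** The item held back until after the 6-month assessment is the workbook. The brochure is a different item, and assessment contact is exempt from the no-contact rule. The two sections are in tension, but both can be true.

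**Can the bias be sized?** No. The article gives neither the brochure's content nor a standard deviation or expected effect for the Care Index. The 0.5 effect size in the sample size section was justified from studies of parental confidence and competence, so it does not carry over to this measure.

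**The case against.** The strongest reply is that the exposure is trivial. It is 2 min per visit against a 600 min programme built on practice and feedback, with the baby alongside and a nappy change before filming of the scored part. The reading looks like a device to keep the mother occupied, and an identical script in both arms is ordinary standardisation. The only other brochures in the article are recruitment brochures spread through clinics, shops and libraries. If this is the same kind of leaflet, it may teach nothing, and both arms could have seen one before randomisation. All of this stands as a reason to expect a small effect. It does not explain why the reading has to be about the programme, since any neutral text would occupy the mother equally well.

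A reader might infer more than the article supports:
- **That the plan breaks its own rule on withholding programme material from controls.** It withholds the workbook; it states no rule about a brochure.
- **That the contrast is diluted by some fraction of the assumed effect.** No such fraction can be derived, and the net sign is open.
- **That the T2 observation is a clean fallback.** It is not, because the brochure is read before T2 scoring too.
- **That coders knew the allocation.** The article does not say so. It describes them as independent and unaware of the aims, and the full protocol may say more.

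**Conclusion.** The concern holds in a limited form. The script places programme-branded reading 3 min before the scored play at both visits, and the text gives no reason to think that controls are spared it. This is an avoidable weakness in the only observer-rated outcome, and a possible though speculative influence on T3 measures in controls.

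The size and direction of any bias are unknown, and the bias may be small. The conclusion rests on two assumptions: that the single script applies to both arms, which is well supported but inferred, and that the brochure says enough about the programme to inform or remind a mother, which the article neither shows nor rules out. Primary outcomes at T2 are not shown to be affected; the article does not say whether the T2 questionnaires come before or after the visit.

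**What to change.** **In the script:** replace the brochure with neutral reading of the same length, unrelated to parenting or to the programme, in both arms. Require Care Index coders to be masked to allocation as well as to the study aims. This changes one line of the visit script and one of the coder instructions, and adds no procedure or staff.

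**For this trial:** the Discussion states that follow-up data collection was completed in January 2016, so the visits cannot be changed. What remains is to code the videotapes masked to allocation and to report three things: what the brochure contained, that both arms read it before scoring at T2 and T3 (or, if the arms differed, which mothers did), and how coders were masked. The cost is control over the information that reaches the coders, recoding if the tapes were already scored with allocation known, and a few sentences in the results paper.

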#### Baby outcomes

The *Baby Behaviour Inventory* [BBI; 80] measures the extent of a range of behaviors that parents often find challenging during the first twelve months. In addition, it captures the level of parental confidence in dealing with the behavior. Encompassing 14 items, parents indicate how often certain behaviors occur. Parents are then asked to identify whether they have experienced the behavior as a problem with their baby using a yes/no format. If the behavior is rated as a problem, parents are asked to rate their confidence in dealing with the behavior. The overall intensity scale of the BBI was found to have satisfactory internal consistency (α = .76) and has demonstrated construct validity to the EPDS and the MSES [81].

The *Baby Diary* [82] was modelled on other similar diaries used in previous studies. We will ask parents to fill in a diary for a 24­hour period to identify the pattern of feeding, sleeping, crying and contentedness in babies. Parents will mark the dominant behavior using specific symbols for each of the four behaviors for 48 half-hour time periods from 6 am to 6 am the following day. Only one diary will be completed per time point so that either mother or father can complete it or they can complete it together.

